## Abstract

**Background:**

Chronic cancer-related pain (CRP) can have a significant negative impact on quality of life. Mindfulness is hypothesized to mitigate chronic CRP by regulating both physical and emotional resistance to pain. In recent years, there has been interest in the use of virtual reality (VR) to deliver mindfulness meditation. VR provides an immersive and engaging environment, which may enhance one's focused attention to present-moment experiences, potentially making mindfulness less effortful and more efficacious for individuals with chronic pain. There has been little research in this area for people with a history of cancer.

**Objective:**

The aim of this mixed methods study is to evaluate the feasibility of a VR-guided mindfulness (VRGM) intervention offered to adult cancer survivors with chronic CRP.

**Methods:**

This mixed methods feasibility study will employ a single-arm, pretest-posttest design with semistructured interviews. In total, 15 cancer survivors will be enrolled in a 6-week home-based intervention that consists of 10–15 min of daily VRGM practice. The primary outcome is feasibility as assessed by accrual rates, retention in the study, intervention adherence, questionnaire completion, and side effect rates. Participants will be assessed on psychosocial outcome measures (i.e., pain, sleep, depressive and anxiety symptoms, fatigue, quality of life, and mindfulness) before and after the intervention, and 6 weeks post intervention (follow-up). Changes in pain will be described in relation to levels of immersion and presence in the virtual environment, trait mindfulness, and amount of VRGM practice. Qualitative information will provide subjective detail on participants’ experience with VRGM to complement quantitative data. This study has been approved by the Health Research Ethics Board of Alberta Cancer Committee (HREBA.CC-20-0411).

**Conclusions:**

This novel intervention provides a potential alternative treatment to pharmacological pain management. Results from this study may inform future larger VGRM trials for chronic CRP to help reduce suffering in people with cancer. Study findings will be disseminated through open access publications, traditional conference presentations, professional cancer organizations, and social media platforms.

## Introduction

1

### Background

1.1

Improved survival owing to advances in cancer treatment has resulted in increased numbers of patients experiencing chronic pain (1), defined by the International Association for the Study of Pain as “persistent or recurrent pain lasting longer than 3 months” (2). The prevalence of chronic cancer-related pain (CRP) has been estimated at 30%–50% in patients undergoing cancer treatment and more than 70% in patients with advanced, metastatic, or terminal disease (3). CRP is often felt as moderate or severe. A 2016 systematic review on the prevalence of CRP (3) found that 38% of 32,261 patients across 52 studies reported at least moderate CRP, while a 2009 European survey study (4) indicated that of 5,084 adults with cancer, 56% reported moderate to severe CRP.

CRP can be due to the cancer itself or its treatment. CRP directly related to cancer can arise from tumor invasion that can affect the viscera, nerves, and bones (5). CRP related to treatment is generally due to peripheral neuropathy from chemotherapeutic agents (e.g., vincristine and taxane), radiotherapy-induced neural damage, and chronic postsurgical pain from mastectomy, amputation, or thoracotomy (5). Certain treatments for cancer, such as head and neck radiation or conditioning regimens administered prior to hematopoietic cell transplant, can also cause painful gastrointestinal mucositis (6).

CRP is associated with psychological distress and functional impairment. One study of 667 individuals with various cancer types found that pain, when present, interfered with participants’ daily activity and enjoyment of life to a moderate to severe extent (7). To this end, chronic pain research often emphasizes the importance of managing pain interference in addition to pain intensity in order to improve quality of life (8). Descriptive studies of women with breast cancer also link pain to poor emotional, physical, and social functioning, in addition to increased fatigue, anxiety, depression, and insomnia (9, 10). Studies also support the link between poor sleep and increased risk for chronic diseases and mortality (11, 12). Therefore, effective treatment of CRP can have broad positive effects on the health and well-being of patients with and survivors of cancer by improving other symptoms related to quality of life and morbidity.

Opioid analgesics are the standard of care for people with chronic CRP (13), but they are limited by negative side effects and neuroadaptations associated with long-term use, which reduces analgesic efficacy (14). Some psychological and physical therapies (e.g., cognitive behavioral therapy, hypnosis, and acupuncture) have shown the potential to reduce levels of CRP as a stand-alone treatment or an adjunct to pharmacological interventions (15, 16). In light of the high prevalence of CRP among patients with and survivors of cancer and the limitations of currently existing treatments, the establishment of safe and effective nonpharmacological interventions for chronic CRP management should be a research priority.

One style of training in mindfulness meditation is a psychological approach that involves directing focused attention to the internal and external experiences occurring in the present moment with an accepting attitude (17, 18). By bringing attention to the present moment, one can cultivate a nonjudgmental awareness to everyday situations that may be perceived as stressful (17). This is particularly important for people with chronic CRP, as pain persistence itself may cause stress (19). It has been hypothesized that mindfulness practice over time would enhance trait mindfulness (i.e., one’s predisposition to be mindful in daily life) and consequently potentially improve pain outcomes by regulating emotional reactions to pain and enhancing acceptance-related coping approaches (20, 21). The biological mechanism explaining this effect with the most supportive evidence is that endogenous opioid pathways mediate the analgesic effects of mindfulness on pain through orbitofrontal cortex activation and thalamic deactivation (22).

A pioneering 1985 single-group study of mindfulness-based stress reduction (MBSR) by Kabat-Zinn (23) showed a significant reduction in chronic pain among 90 patients with a variety of conditions, even up to 4 years post intervention (24). More recent randomized controlled trials (RCTs) have also supported the positive effects of mindfulness on chronic pain (25). For example, in a 2011 RCT of people with irritable bowel syndrome (IBS) (26), participants reported significant pain improvement following a mindfulness-based intervention, and benefits were maintained 3 months post intervention. Multivariate path analyses suggested that mindfulness practice mitigated pain through improving anxiety and emotional responses to IBS symptoms (26, 27). While very few mindfulness studies targeting pain have been conducted among cancer survivors, the evidence to date is promising with studies showing small to moderate effects (28). For example, in a 2016 RCT (29) comparing MBSR to an active control condition (psychoeducational support) for breast and colorectal cancer survivors, MBSR participants reported significant reduction in pain compared with control participants (Cohen *d *= 0.53).

In the past few years, there has been a growing interest in using virtual reality (VR), a computer-generated 360° representation of a virtual environment displayed through a headset as a medium to support mindfulness practice (30). The multisensory information and stereo-visual image that VR delivers are meant to create a sense of space and depth, which can help users become fully present and immersed in the virtual atmosphere (31). Immersion is the degree to which the technological features of VR systems deliver an extensive, inclusive, surrounding, and vivid illusion of reality to the senses of a human participant, whereas presence is the perception of being present in a VR environment (i.e., a feeling of being there) (32). Although other platforms that provide guidance on mindfulness (e.g., web-based interventions or videos and smartphone apps) are available, environmental distractions (e.g., noisy surroundings) may pose limitations. VR has the potential to address those challenges by providing an engaging and immersive environment, potentially leading to sustained mindfulness and larger effects for reducing CRP (33).

Because humans have a limited amount of available conscious attention, VR competes for attention otherwise directed toward interpreting stimulation from the real environment, leaving lesser cognitive capacity available for processing external distractions (31, 33). It is also possible that VR-guided mindfulness (VRGM) can help participants self-initiate and continue mindfulness practice, as well as maintain conscious and cognitive efforts required for effective practice, all of which have previously been identified as barriers to mindfulness meditation practice, particularly among novice meditators (30, 33).

VRGM has the potential to overcome some of the limitations of traditional mindfulness-based interventions, such as MBSR, that involve an instructor within a group setting. External distractions from other group members may pose limitations required for effective mindfulness practice. Regularly attending sessions may be difficult for cancer patients and survivors with chronic pain due to pain related interference with daily activity, hospitalizations, or cancer treatments, in addition to personal commitments. The timing and frequency of sessions may not meet the meditative needs of participants. For example, some may prefer morning meditations to energize oneself, while others may prefer evening meditations to relax before sleep. A weekly session may not suffice the needs for people with cancer experiencing chronic pain, who may desire to practice mindfulness daily or multiple times per day for pain management. Those living in remote areas may have difficulties with accessibility, as local mindfulness-based interventions may not be available. Additional accessibility barriers may occur due to costs associated with attending sessions (i.e., session fees, transportation, parking, etc.), especially in countries without universal healthcare. VRGM has the potential to overcome these challenges by eliminating external group distractions and providing more flexibility in the timing, frequency, and accessibility of mindfulness practice through a self-delivered intervention.

In the last 10 years, innovations in technology have dramatically driven down costs for development and implementation of VR, which has given rise to its commercialization and affordability as a cost-effective tool for clinical practice (34–36). For example, in the 1990s VR systems used in clinical research could cost up to $90,000 USD, and today in 2024 the Meta Quest 2 standalone VR headset can be purchased for $250 USD (37). Major milestones for VR technology occurred in 2016 when companies in the technology industry began mass producing VR headsets and in 2019 when the industry shifted towards the development of standalone VR headsets (a wireless, easy to use, self-contained VR system not requiring an external computer to run the software) (34). Continued investment in VR technology by big tech companies, such as Meta, Apple, Microsoft, and Google, driven by competition for potentially new lucrative VR-related markets, have resulted in a considerable increase in the image quality and immersive experience year-over-year, while continuously improving affordability and availability (34). However, the current cost of a VR headset may still be financially constraining for some, and as such an ideal scenario to improve accessibility would have cancer support centres purchase a small number of VR headsets for people with cancer to use freely within the centre.

Despite its potential benefits for patients with chronic CRP, VRGM has received relatively limited attention in the VR literature. VR has primarily been used as a distraction technique for acute procedural pain relief, with some studies incorporating video games or virtual traveling into the VR experience as a way to enhance psychological distraction and reduce self-reported pain (31). Importantly, very few studies targeting chronic pain used VR as a medium to facilitate mindfulness meditation, which is less about distraction and more about awareness of current experience. A 2015 RCT of 13 participants (33) found VRGM to be superior to a mindfulness audio track alone in reducing chronic noncancer pain symptoms. Similarly, in a 2017 single-group study (38) evaluating the benefits of VRGM for 18 participants with chronic pain (16 patients with cancer and 2 patients with neurological conditions), all participants reported a reduction in pain intensity, ranging from a 20% to a 100% reduction.

Taken together, while VRGM could be a novel promising approach for chronic CRP management, additional research is needed to evaluate its efficacy and determine its acceptability and feasibility to guide the design and implementation of future trials. Research is also needed to understand the potential mechanisms of mindfulness-related improvement in pain intensity and pain interference and to test VRGM models that are self-deliverable and home-based to enhance effectiveness and sustainability. As a first step in a program of research, this mixed methods single-group feasibility study will evaluate a home-based 6-week VRGM intervention for cancer survivors with CRP lasting longer than 3 months. The following paragraphs outline the specific study objectives.

### Primary objective

1.2

#### Objective 1: to evaluate the feasibility of a self-administered, at-home, 6-week VRGM program for chronic CRP

1.2.1

Feasibility outcomes include recruitment rates, intervention adherence, and study completion rates, as well as intervention safety as determined by the occurrence, type, and severity of negative side effects.

### Secondary objectives

1.3

#### Objective 2: to explore the potential benefits of a 6-week VRGM program for patients with chronic CRP

1.3.1

To address this proof-of-concept objective, effect sizes and confidence intervals of changes in outcome measures (pain, sleep, depressive and anxiety symptoms, fatigue, quality of life, and analgesic use) will be described across different time points.

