#### Eligibility criteria

2.2.2

Patients with any type or stage of cancer, who have reported chronic CRP (i.e., for 3 months or longer), are eligible to participate. Patients could be on active treatment, posttreatment, or receiving palliative care (see Table 1 for rationale of all inclusion and exclusion criteria).

**Table 1 T1:** Eligibility criteria.

Criteria	Rationale
Inclusion	
Chronic cancer-related pain. Specifically, one screening question will be used: “Do you have bodily pain related to cancer or as a result of cancer treatment that has lasted for more than three months?” (Answer must be yes to proceed with eligibility assessment)	This criterion is consistent with the chronic pain definition by the International Association for the Study of Pain (2).
Moderate to severe pain interference with function, as indicated by a score of >3 on the Brief Pain Inventory-pain interference with daily activities 10-point Likert scale (0 = “does not interfere” and 10 = “interferes completely”) (49)	Interventions targeting chronic pain often aim to improve both pain intensity and pain-related functional impairment (16).
Cancer diagnosis (all stages)	This criterion is intentionally broad to enhance generalizability.
Ability to speak and read in English	Mindfulness audio narrative and study assessments will be in English.
Exclusion	
Patients with dementia, Alzheimer disease, intellectual disability, amnesia, schizophrenia, psychosis, or with a history of seizures or epilepsy	People with pre-existing neuropsychological conditions may be at high risk for adverse events (e.g., confusing virtual reality with real world) (50).
Severe vision or hearing problems	This study involves prerecorded audio instructions of mindfulness techniques and a 3D virtual reality experience, requiring adequate visual and hearing ability.
Recent change (i.e., in the 2 weeks prior to study enrollment) or a planned change in opioids or antidepressants during the 6-week study period	Pain and antidepressant medications can affect pain scores during the study. While this feasibility study does not aim to evaluate efficacy, inclusion criteria are meant to be comparable to those that would be used in an efficacy trial.

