### Outcome measures

2.7

All the study measures are described in Table 4 (51–65). Standardized measures of pain, sleep, depressive and anxiety symptoms, fatigue, and quality of life (objective 2), as well as trait mindfulness and levels of immersion and presence in the VR experience (objective 3), will be used. Sociodemographic and medical information collected from participants at baseline will include age, sex, gender, race and ethnicity, cancer type and stage, time since diagnosis, time since last treatment, presence and severity of comorbidities, educational level, marital status, occupational status, and type and frequency of nonpharmacological interventions used for pain in the last 3 months. The prescribed analgesic regimen (standing and as needed) will also be obtained. This will include the number of analgesics prescribed, types of analgesics, frequency of administration, route of administration, and prescribed dose. The entire battery of questionnaires has been user-tested and requires approximately 30 min to complete.

**Table 4 T4:** Outcome measures.

Construct	Measure	Description
Pain		
Pain intensity	Numeric pain rating scale (51, 52)	0–10 Likert Scale (0: no pain at all; 10: worst possible pain); widely used and validated in oncology (51, 52)
Pain severity and interference	Pain questionnaire (53, 54)	7-item scale that assesses pain frequency, location, duration, intensity, and emotional upset due to pain in the past 7 days. This scale has demonstrated good validity and reliability coefficients (53, 54).
Pain catastrophizing	Pain catastrophizing scale (55)	13-item questionnaire that assesses on a 5-point scale, ranging from 0 (not at all) to 4 (always), to which degree one experiences certain thoughts or feelings during pain over the past 7 days. Studies have supported the psychometrics of this scale (55).
Neuropathic pain quality	PROMIS^a^ Neuropathic Pain Quality (56)	5-item scale that assesses neuropathic pain over the past 7 days; used to distinguish between neuropathic and non-neuropathic pain conditions. PROMIS-Pain Quality-Neuro has demonstrated good psychometric properties (Cronbach's alpha = 0.87) (56).
Pain interference	PROMIS-SF^b^-8a-pain interference (57)	8-item scale that assesses pain interference with function in the past 7 days. Items are scored on a 1–5 scale. Alpha reliability ranges from .96 to .99 and construct validity (57).

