Analgesic use	Investigator-developed	Daily analgesic use log including the name, dosage, and frequency of all pain medications.
Virtual reality experience		
Immersion	1–10 likert scale add-on to the immersive experience questionnaire (IEQ) (58)	One 1–10 Likert scale that rates how immersed did a participant feel during VR (1 = not at all immersed, 10 = very immersed). The psychometrics of the IEQ questionnaire has been evaluated in a general population study of 260 participants with high reliability and validity coefficients (58).
Presence	Slater-usoh-steed (SUS) questionnaire (59)	3-item 1–7 Likert-scale questionnaire that evaluates presence (i.e., the sense of being in a VR; the extent to which a VR feels real; and the extent to which a VR is thought of as a place visited). The SUS questionnaire has demonstrated good psychometric properties in various populations with well-established concurrent validity with other measures of VR presence (59).
Sleep		
Sleep quality	Pittsburgh sleep quality index (PSQI) (60)	PSQI includes 19 items grouped into 7 subscales: (1) sleep quality, (2) sleep efficiency, (3) daytime dysfunction, (4) sleep latency, (5) sleep disturbances, (6) sleep duration, and (7) use of sleep medication. Items are scored on a 0–3 scale. PSQI has demonstrated adequate reliability and validity among cancer patients, with Alpha reliability coefficients ranging from .70 to .80 (60).
Sleep amount and quality, pain interference with sleep	Sleep diary (61)	A sleep diary that is well-validated for use with chronic pain patients. It assesses one's previous night's sleep, including the number of hours slept, sleep onset latency, number of awakenings, sleep quality (Likert scale; 0 = “extremely poor” to 5 = “extremely good”), and sleep restfulness (Likert scale; 0 = “not at all rested” to 5 = “well rested”) (61), as well as one's level of pain at bedtime and upon awakening on a 6-point Likert scale (0: no pain at all; 5: very intense pain) (61, 62)
Depression and anxiety symptoms		
Anxiety	PROMIS-SF-8a-anxiety (63)	8-item scale that measures anxiety over the past 7 days. Items are scored on a 1–5 scale. PROMIS-SF-anxiety scale has shown excellent convergent and discriminate validity with other measures, with a Cronbach's alpha of .95 (63).

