### Timing of assessments

2.8

Timing of assessments is fully described in Table 5 (schedule of measures).

**Table 5 T5:** Schedule of measures.

		Treatment and follow-up							
	Enrollment	Baseline	1 week	2 weeks	3 weeks	4 weeks	5 weeks	6 weeks	12 weeks
Education and consent	X								
Screening checklist	X								
Demographic questionnaire and medication history	X								
Objective 1 (feasibility)									
Home practice log			D^a^	D	D	D	D	D	
Objectives 2 and 3 (benefits and factors)									
Pain Numeric rating scale (scores 0–10)^b^			D	D	D	D	D	D	
Immersive Experience Questionnaire^b^			D	D	D	D	D	D	
Slater-Usoh-Steed scale^b^			D	D	D	D	D	D	
Analgesic use log			D	D	D	D	D	D	
Sleep diary^c^		X						X	X
PROMIS^d^-Short form–pain interference scale		X	X	X	X	X	X	X	X
Pain questionnaire		X						X	X
Pain catastrophizing scale		X						X	X
PROMIS neuropathic pain quality		X						X	X
Pittsburgh sleep quality index		X						X	X
PROMIS-short form–anxiety scale (8a)		X						X	X
PROMIS-short form–depression scale (8a)		X						X	X
PROMIS-short form–fatigue scale (8a)		X						X	X
EORTC QLQ-C30^e^ (2 likert scales with scores of 0–10)		X						X	X
Five-facet mindfulness questionnaire–short form		X						X	X

^a^
D: daily completion over the course of the entire study through week 6.

^b^
Responses on the Pain Numeric Rating Scale, Immersive Experience Questionnaire, and Slater Usoh-Steed Scale are recorded using the virtual reality device.

^c^
Participants will maintain a sleep diary for 1 week at baseline, post intervention, and 6 weeks post intervention (12 weeks).

^d^
PROMIS, patient-reported outcomes measurement information system.

^e^
EORTC QLQ-C30, European organization for the research and treatment of cancer quality of life questionnaire.

#### Objective 2

2.8.1

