Psychosocial outcome measures (i.e., pain, sleep, fatigue, depressive and anxiety symptoms, and quality of life) will be assessed before and after the intervention and 6 weeks post intervention (follow-up). As noted above, pain-related functional impairment is often a priority in chronic pain mitigation efforts and is thus an important outcome for this feasibility trial. Therefore, pain interference with function will be assessed weekly during the 6-week intervention period and then again at follow-up. The VR device will record the intensity of participants’ pain on a Numeric Rating Scale (scores of 0–10) (51) before and immediately after each VRGM session. Participants will maintain analgesic use in the home practice logs to record their use of pain medications and dosages daily, until completion of the 6-week VRGM intervention. Additionally, they will maintain a sleep diary for 1 week before and after the intervention, as well as at 6 weeks post intervention (follow-up), including assessments of sleep duration and quality and pain interference with sleep. Since sleep diaries evaluate sleep on a daily basis, many of the limitations of retrospective self-reported sleep measures are minimized, such as recall bias and recency bias (tendency to recall last few nights) (66).

#### Objective 3

2.8.2

The VR device will record participants’ level of immersion and presence in each VRGM session. Trait mindfulness will be evaluated before and after the intervention and 6 weeks post intervention (follow-up).

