## Conclusions

4

Survivors of cancer experience increased levels of psychosocial symptoms and pain interference. This novel intervention provides a potential alternative treatment to opioid analgesics. Results from this study may inform future larger VGRM trials for chronic CRP to help reduce suffering in people with cancer.

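### Change in analgesic use is an Objective 2 outcome, but actual use is logged only in weeks 1 to 6, so neither a like-for-like pre-post change nor a follow-up change can be computed

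*Protocol article*

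**What the plan says.** Section 1.3.1 sets out Objective 2 as "effect sizes and confidence intervals of changes in outcome measures (pain, sleep, depressive and anxiety symptoms, fatigue, quality of life, and analgesic use", and adds that these "will be described across different time points". Analgesic use is thus one of the named change outcomes.

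The instrument is defined in Table 4 (section 2.7): "Daily analgesic use log including the name, dosage, and frequency of all pain medications". Its timing is given twice. In Table 5 the row "Analgesic use log" carries the daily mark in weeks 1 to 6 only. In section 2.8.1 participants are to "record their use of pain medications and dosages daily, until completion of the 6-week VRGM intervention".

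Before the intervention, section 2.7 provides that "The prescribed analgesic regimen (standing and as needed) will also be obtained", with the number and types of drugs, frequency, route and prescribed dose. Table 5 also has a medication history, marked at Enrollment only.

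Two other lists bear on the point. Section 2.8.1 names the outcomes measured before, after and 6 weeks after the intervention, and section 2.9.1 names those whose changes get effect sizes and confidence intervals. Both give pain, sleep, fatigue, depressive and anxiety symptoms, and quality of life. Neither includes analgesic use.

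**The concern.** A change outcome needs the same quantity measured at both ends of the interval. For analgesic use, the protocol measures intake only while participants are on the intervention. Objective 2 asks about the possible benefits of the programme, so the natural reference is intake before it starts, and that is not collected. Nor is intake at the 12-week follow-up.

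This is a matter of data collection, not of analysis detail. A statistical analysis plan can choose a summary measure or a method, but it cannot supply a pre-intervention week that was never logged. Section 2.8 presents Table 5 as the full schedule, and the text of section 2.8.1 agrees with it, so the gap is not an accident of condensing the article.

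There is a secondary consequence for pain. The rationale column of Table 1 accepts that medication can affect pain scores, and the exclusion there covers a "planned change in opioids or antidepressants during the 6-week study period". Pain outcomes run on to week 12, and no analgesic information is scheduled after week 6. The 12-week pain changes will have to be described without knowing whether intake changed in between.

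**Working it through.** No arithmetic in the plan needs reproducing: the protocol gives no figure for analgesic use. The check sets the objective against the schedule.

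**Step 1: what each Objective 2 outcome has in Table 5.**

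| Outcome named in 1.3.1 | Baseline | 6 weeks | 12 weeks |
|---|---|---|---|
| Pain (pain questionnaire, catastrophizing, neuropathic quality, PROMIS interference) | yes | yes | yes |
| Sleep (PSQI, diary) | yes | yes | yes |
| Depressive symptoms | yes | yes | yes |
| Anxiety | yes | yes | yes |
| Fatigue | yes | yes | yes |
| Quality of life | yes | yes | yes |
| Analgesic use (daily log) | no | yes, as part of weeks 1 to 6 | no |

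Six of the seven named outcomes have a measure at all three points. Analgesic use is the only one that does not.

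**Step 2: which changes can be computed.** Write U0 for intake before the intervention, U1 and U6 for intake in weeks 1 and 6, U12 for intake at follow-up, and P0 for the prescribed regimen at entry.

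- Pre-post change: U6 − U0 = (U6 − U1) + (U1 − U0). The first bracket is observed. The second is not, because U0 is not logged. Any change that happens by or during week 1 falls in the unobserved bracket.
- Follow-up change: U12 − U0 and U12 − U6 both need U12, which is not recorded.
- Change within the intervention: U6 − U1 is available, with a reference week already on intervention.

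**Step 3: can P0 stand in for U0?** For standing medication taken as prescribed, P0 is a reasonable approximation. For as-needed drugs it is not, since the prescription allows a range of intake and does not say how much was used. The scope differs too: the log covers all pain medications, while section 2.7 describes the regimen as what was prescribed. U6 − P0 therefore mixes real change with the gap between prescription and intake. P0 is also not scheduled again, so a change in prescription is not available either.

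**Step 4: do the lists agree?** Section 1.3.1 includes analgesic use among the change outcomes; the list in section 2.9.1, introduced as a complete one, does not. Section 2.8.1 covers the analgesic log under Objective 2 but leaves it out of the set measured before, after and at follow-up.

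**Step 5: added burden of the repair.** The log now runs 6 × 7 = 42 days. Two added weeks give 42 + 14 = 56 days; three give 42 + 21 = 63 days. Which applies depends on whether the post-intervention sleep-diary week falls within week 6 (Table 5 marks it there) or after it (section 2.8.1 places it after the intervention).

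**The case against.** The best defence is that section 1.3.1 does not say which time points it means. It never promises a baseline-to-week-6 or baseline-to-week-12 contrast for analgesic use, and a change across weeks 1 to 6 meets its letter. Section 2.8.1 handles the log separately from the outcomes measured before, after and at follow-up, which may be deliberate. This stands in part: a reader might infer that specific planned contrasts have been lost, but the protocol does not state any for this outcome. What remains is that the one available change starts on treatment, which serves an objective about benefit poorly.

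A reader might also infer that there is no baseline information at all. That goes too far. The regimen and medication history are recorded at entry, and Table 1 excludes recent opioid or antidepressant changes in the 2 weeks before enrollment. For standing drugs this is a usable reference; for as-needed intake it is not.

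A third tempting reading is that the 12-week pain change is meaningless. It can be computed, since pain measures are scheduled at Baseline and 12 weeks. The missing analgesic record makes it harder to interpret, but attribution is already limited by the single-arm design, which section 3.1 declares.

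Finally, a reader might hold the gap against the statement in section 4, "This novel intervention provides a potential alternative treatment to opioid analgesics". That sentence speaks of potential, is followed by a reference to future larger trials, and is not offered as a result of the log. It is a separate matter and gives this point no support.

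**Conclusion.** The point holds as a mismatch between a stated objective and the measurement schedule. Followed exactly, the plan yields no like-for-like pre-post change in analgesic use and no follow-up change. It yields only a within-intervention change whose first week is already on treatment. The outcome lists in sections 1.3.1 and 2.9.1 conflict, and section 2.8.1 sides with the latter in leaving analgesic use out of the repeated outcomes.

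Its weight is moderate. One secondary outcome of seven is affected, in a descriptive feasibility study of 15 participants. Accrual, retention, adherence, questionnaire completion and side-effect rates are unaffected.

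The conclusion assumes that Table 5 and section 2.8.1 state the whole collection schedule for analgesics, as section 2.8 indicates, and that the regimen taken at entry records prescription and not intake, as section 2.7 words it.

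**What to change.** Preferred change:

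- Attach the existing analgesic use log to the one-week sleep-diary periods at baseline and 12 weeks, and mark those cells in Table 5. The log now sits inside the home practice log, which does not exist in those weeks, so it needs its own sheet or a column in the diary.
- State whether the post-intervention diary week lies within week 6 or after it. If after, carry the log into that week as well.
- Add analgesic use to the outcome lists in sections 2.8.1 and 2.9.1.
- Show the 12-week pain changes next to the recorded change in analgesic use, descriptively.

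Cost: two to three extra weeks of brief logging per participant, in weeks when a daily diary is already kept, plus edits to one table and two lists. No new instrument or visit is needed. It has to be settled before participants start, because a missed baseline week cannot be recovered.

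Minimum alternative, with no added burden: restrict the analgesic outcome in section 1.3.1 to change within weeks 1 to 6, say that the reference week is on intervention, and reconcile sections 1.3.1, 2.8 (Table 5), 2.8.1 and 2.9.1. This makes the plan consistent but gives up the pre-post and follow-up changes.
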